# A double-blind, randomized controlled trial to compare the effect of biannual peripheral magnetic resonance imaging, radiography and standard of care disease progression monitoring on pharmacotherapeutic escalation in rheumatoid and undifferentiated inflammatory arthritis: study protocol for a randomized controlled trial

**DOI:** 10.1186/1745-6215-15-268

**Published:** 2014-07-05

**Keywords:** Arthritis, Rheumatoid, Randomized control trial, Magnetic resonance imaging, Radiography, Antirheumatic agents, Disease management

## Abstract

**Background:**

Permanent joint damage is a major consequence of rheumatoid arthritis (RA), the most common and destructive form of inflammatory arthritis. In aggressive disease, joint damage can occur within 6 months from symptom onset. Early, intensive treatment with conventional and biologic disease-modifying anti-rheumatic drugs (DMARDs) can delay the onset and progression of joint damage. The primary objective of the study is to investigate the value of magnetic resonance imaging (MRI) or radiography (X-ray) over standard of care as tools to guide DMARD treatment decision-making by rheumatologists for the care of RA.

**Methods:**

A double-blind, randomized controlled trial has been designed. Rheumatoid and undifferentiated inflammatory arthritis patients will undergo an MRI and X-ray assessment every 6 months. Baseline adaptive randomization will be used to allocate participants to MRI, X-ray, or sham-intervention groups on a background of standard of care. Prognostic markers, treating physician, and baseline DMARD therapy will be used as intervention allocation parameters. The outcome measures in rheumatology RA MRI score and the van der Heijde-modified Sharp score will be used to evaluate the MRI and X-ray images, respectively. Radiologists will score anonymized images for all patients regardless of intervention allocation. Disease progression will be determined based on the study-specific, inter-rater smallest detectable difference. Allocation-dependent, intervention-concealed reports of positive or negative disease progression will be reported to the treating rheumatologist. Negative reports will be delivered for the sham-intervention group. Study-based radiology clinical reports will be provided to the treating rheumatologists for extra-study X-ray requisitions to limit patient radiation exposure as part of diagnostic imaging standard of care. DMARD treatment dose escalation and therapy changes will be measured to evaluate the primary objective. A sample size of 186 (62 per group) patients will be required to determine a 36% difference in pharmacological treatment escalation between the three groups with intermediate dispersion of data with 90% power at a 5% level of significance.

**Discussion:**

This study will determine if monitoring RA and undifferentiated inflammatory arthritis patients using MRI and X-ray every 6 months over 2 years provides incremental evidence over standard of care to influence pharmacotherapeutic decision-making and ultimately hinder disease progression.

**Trial registration:**

This trial has been registered at ClinicalTrials.gov: NCT00808496 (registered on 12 December 2008).

## Background

Inflammatory arthritis (IA) affects up to 3% of the adult population [1]. It is comprised of the following specific diagnoses: ankylosing spondylitis, psoriatic arthritis, reactive arthritis, rheumatoid arthritis (RA), inflammatory osteoarthritis and undifferentiated IA (UIA). Of these forms, RA is most common with a prevalence ranging from 0.5 to 2.0% with a commonly accepted figure of 1% [2,3].

Early in the disease course, RA results in pain, joint swelling and stiffness, fatigue, and functional disability [3-5]. In the long term, the majority of RA patients suffer permanent erosive joint damage, increased risks for cardiovascular and systemic comorbidities, and a higher mortality rate [6-8]. Joint destruction begins early in the disease course [9-13]. Within 3 years from symptom onset, up to 90% of patients develop irreversible joint damage [12,13]. Various studies have demonstrated that magnetic resonance imaging (MRI) is more sensitive than radiography (X-ray) at detecting early articular changes leading to and including erosive joint damage [14-17].

Erosive disease on X-ray is the classic hallmark of longstanding, destructive RA [18,19]. The second notable X-ray prognostic feature is joint space narrowing (JSN) [20,21]. Although erosions have been linked to physical deformity and long-term functional declines [22], more recent data suggest that JSN may have a greater relative effect on these outcomes in disease subsets [23].

In contrast, RA pathological features measured on MRI using the Outcomes in Rheumatology (OMERACT) RA MRI Score (RAMRIS) include synovitis, bone marrow edema, and erosions [24]. Synovitis is a precursor to bone marrow edema [25] and both predict erosions [26-28]. Cross-sectionally, erosions on MRI do not correlate well with X-ray erosions [29,30]. Erosions on MRI may represent bone lesions at an earlier stage of development below the lower limit of detection of X-ray. With time, MRI lesions may increase in size to be detected on X-ray [30-32]. Early in the development of OMERACT RAMRIS the decision was made not to measure other notable features including, but not limited to, tenosynovitis and JSN [33].

Limiting disease progression on diagnostic imaging remains an important clinical and regulatory outcome [34]. Early pharmacologic treatment of RA with conventional and biologic disease-modifying anti-rheumatic drugs (DMARDs) has proven to improve clinical [35-38] and radiological [38] outcomes. Treat-to-target strategies of maintaining low disease activity using anti-rheumatic drug augmentation have also been demonstrated to improve clinical outcomes in patients [39]. Despite optimal control of clinical and laboratory findings, erosive disease progression may continue to progress for subsets of the disease population [17]. These data suggest that diagnostic imaging may complement pharmacotherapeutic decision-making. However, diagnostic imaging is infrequently and unsystematically applied to routine disease management [40]. Disease monitoring with sensitive and responsive imaging modalities may help to augment therapy and further delay disease progression.

The primary objective of the study is to investigate the relative value of MRI or X-ray over standard of care as tools to guide DMARD treatment decision-making by rheumatologists for the care of RA and UIA. Specifically, the study compares the effect of biannual monitoring of disease progression with: 1) 1.0 T extremity MRI of the second to fifth metacarpophalangeal joints (MCPs) of the worst-affected hand at baseline; 2) X-rays of both hands and wrists; and 3) standard of care on the rate of augmenting DMARD treatment decision-making over 2 years. The co-primary objective aims to determine differences in diagnostic imaging evidence of disease progression with biannual monitoring using MRI or X-ray over standard of care over 2 years.

Secondary, exploratory objectives include the following. The effect of intervention-based pharmacotherapeutic augmentation on diagnostic imaging evidence of disease progression, composite measures of disease activity, function, and quality of life will be determined. The difference in the frequency of changes detected between the two active interventions will be determined. The effect of study participation bias on the standard of care frequency of diagnostic imaging usage in disease management of the population will be determined. Healthcare resource utilization (for example, number of physician visits, hospitalizations) and productivity losses for this population and across study groups will be investigated. Blinded, biannual in-term assessments of these outcomes will also be investigated.

## Methods/design

### Study design

The study is a three-group, double-blind, randomized controlled trial (Figure 1). The interventions include 1.0 T extremity MRI of the second to fifth MCPs of the worst-affected hand (determined by cumulative swollen and tender joint count at baseline) and X-ray of both hands using lateral, anteroposterior, and oblique views. The two interventions will be superimposed on standard of care. All groups, including the sham-intervention group, will receive standard of care diagnostic imaging feedback. Participants will be assigned to one of the three interventions using minimization, also known as baseline adaptive randomization [41,42]. The prognostic factors for intervention allocation were determined from recent American College of Rheumatology anti-rheumatic treatment recommendations [43]. Intervention allocation will be concealed by having all study participants undertake both diagnostic imaging scans at all time points: one-third will have positive or negative reports of disease progression reported back to the rheumatologist based on MRI scores; one-third will have X-ray-based results reported; and one-third will always have negative reports returned to the rheumatologist. Study rheumatologists are informed of the study protocol. They are aware that one-third of the negative results will not be based on imaging findings and are allowed to prescribe X-ray diagnostic imaging as part of standard of care. All image sets will be anonymized per assessment and scored independently by one of four radiologists using the van der Heijde-modified Sharp Score (vdHSS) for X-ray [44-46] and a non-contrast modification [47] of the OMERACT RAMRIS for MRI [24]. At the beginning of the study, and mid-way through follow-up, a sample of nine image sets for each modality will be read by all four radiologists to determine the inter-rater smallest detectable difference (SDD).

**Figure 1 F1:**
[figure not shown]
**Study participant flow diagram and intervention allocation prognostic variables.** Anti-CCP, anti-citrullinated cyclic peptide antibodies; BRM, biologic response modifier; DMARD, disease-modifying anti-rheumatic drug; DAS28, 28-joint disease activity score; MCP, metacarpophalangeal joint; MRI, magnetic resonance imaging.

The SDD in imaging scores will be used to adjust for inter-rater reliability in the diagnostic imaging scores. Differences in SDD-adjusted scores will be used to determine disease progression. The analyst determining the SDD will be blinded to patient intervention allocation. Intervention allocation will be concealed from treating rheumatologists by reporting disease progression as changes in SDD magnitudes with follow-up disclosure of neither images, nor imaging features. The selection of the anatomy to compare and the frequency of intervention was based on the following considerations: anatomy most commonly scanned over follow-up in this population [40], least anatomy required to visualize greatest change in disease progression [14,15], and minimization of both radiation exposure for X-ray and MRI scan time.

### Population

Adults with established RA and UIA will be recruited for the study. Subjects fulfilling the Emery and colleagues (2002) early referral to rheumatology recommendation for RA will be included: at least three swollen joints, positive squeeze test for either the MCPs or metatarsophalangeal joints, or at least 30 minutes of self-reported morning stiffness [48]. These criteria are strongly associated with rheumatologic opinion on early IA and strongly associated with DMARD treatment decision-making [49]. Eligible subjects will be at least 18 years of age and have a minimum of 6 weeks of self-reported symptom duration at enrolment.

Subjects fulfilling any of the following criteria will be excluded: history of juvenile idiopathic (or inflammatory) arthritis; rheumatologist-confirmed primary clinical diagnosis of viral arthritis or spondyloarthropathy (ankylosing spondylitis, psoriatic arthritis, reactive arthritis, or inflammatory bowel disease); at the investigator’s discretion, a concomitant condition with medical priority over IA; a concomitant condition that contraindicates treatment with DMARDs (not including sulfa allergy or medically controlled non-terminal liver disease); psychological deficit or diminished capacity to provide independent, informed consent; planned event that prevents study follow-up; extremity MRI scanner contraindications including some joint replacements, stents, pace-makers, neurostimulators, or other metal or electronic implants; other irremovable metallic foreign bodies with magnetic properties or known to interfere with MRI; and a current or historical chronic or high exposure to iron materials.

Study participants will be recruited from the practices of six participating rheumatologists at McMaster University, Hamilton, ON, Canada. The study investigators will prescreen the patients for eligibility and refer them to study staff for the provision of informed consent and enrolment.

### Interventions

Study measures are captured in the schedule of assessments (Table 1). Study participants will attend study visits at weeks 0, 13, 26, 39, 52, 78, and 104. All participants will have MRI and X-ray scans within 4 weeks of biannual study visits from weeks 0 to 104. Clinical assessments, prognosis, and response to pharmacologic treatment will be assessed quarterly during the first year and biannually in the second. Study participants will be accrued over 1 year and followed for 2. At week 0 (baseline) and 104 weeks, all study participants will have an MRI conducted for the second to fifth MCPs of both hands. All participants will also have X-rays of both hands and feet conducted at baseline and 104 weeks.

**Table 1 T1:** Study schedule of assessments

**Assessment**	**Week**						
	**0**	**13**	**26**	**39**	**52**	**78**	**104**
Informed consent	X	X	X	X	X	X	X
OHIP number (each visit)	X	-	-	-	-	-	-
Demographics							
Date of birth	X	-	-	-	-	-	-
Gender	X	-	-	-	-	-	-
Race/ethnicity	X	-	-	-	-	-	-
Dominant hand	X	-	-	-	-	-	-
Household income (socioeconomic status)	X	-	-	-	-	-	-
Pack-years smoked	X	-	-	-	-	-	-
Medical history and comorbidities							
Surgeries	X	X	X	X	X	X	X
Conditions	X	X	X	X	X	X	X
Medications	X	X	X	X	X	X	X
Clinical assessment	X	X	X	X	X	X	X
Symptom duration	X	-	-	-	-	-	-
Morning stiffness duration	X	X	X	X	X	X	X
Swollen joint count	X	X	X	X	X	X	X
Tender joint count	X	X	X	X	X	X	X
Extra-articular features	X	X	X	X	X	X	X
Fatigue	X	X	X	X	X	X	X
Pain – Visual Analog Scale	X	X	X	X	X	X	X
Global physician impression of disease progression	X	X	X	X	X	X	X
Global patient impression of disease progression	X	X	X	X	X	X	X
Diagnostic imaging							
MRI – MCPs 2-5							
Worst-affected hand	-	-	X	-	X	X	-
Both hands	X	-	-	-	-	-	X
Radiography							
Both hands	X	-	X	-	X	X	X
Both wrists	X	-	X	-	X	X	X
Both feet	X	-	-	-	-	-	X
Laboratory tests							
Rheumatoid factor	X	O	O	O	O	O	O
Anti-citrullinated cyclic peptide antibodies level	X	-	-	-	-	-	-
Erythrocyte sedimentation rate	X	X	X	X	X	X	X
C-reactive protein	X	X	X	X	X	X	X
Other	X	X	X	X	X	X	X
Concomitant medications	X	X	X	X	X	X	X
Adverse events	X	X	X	X	X	X	X
Health-related quality of life							
Health assessment questionnaire	X	-	X	-	X	X	X
Health Utility Index Mark 3 and EQ-5D	X	-	X	-	X	X	X
Health resource utilization	X	-	X	-	X	X	X
Work and leisure time productivity	X	-	X	-	X	X	X

X, assessment conducted; O, assessment conducted only if preceding assessment negative.

EQ-5D, EuroQOL general quality of life instrument; MCP, metacarpophalangeal joint; MRI, magnetic resonance imaging; OHIP, Ontario Health Insurance Plan.

### Non-contrast OMERACT RAMRIS

A non-contrast modification of the OMERACT RAMRIS system will be used to follow disease progression on MRI [47] (Figure 2). The OMERACT RAMRIS is an internationally recognized system for measuring RA disease changes on MRI [24,50-53]. The system is comprised of the following components: a definition of the MRI sequences, planes of view, contrast agent requirements, and signal descriptions for each feature and scoring system [24]; image atlas [50]; guidance on pitfalls with the system [51]; and clinometric property validation studies [52,53]. The non-contrast modification pertains to the measurement of synovitis. In the modification, synovitis is detected on MRI without a contrast agent, using Fast Spin Echo, T2-weighted, fat-saturated sequences [47,54-57]. The OMERACT RAMRIS scale remains the same with the modification.

**Figure 2 F2:**
[figure not shown]
**Outcomes in Rheumatology Rheumatoid Arthritis Magnetic Resonance Imaging Score (OMERACT RAMRIS) form for scoring magnetic resonance imaging (MRI) evidence of disease progression.** MCP, metacarpophalangeal joint.

**Figure 3 F3:**
[figure not shown]
**van der Heijde-modified Sharp Score (vdHSS) forms for scoring X-ray evidence of disease progression.** Left: erosion scoring. Right: joint space narrowing (JSN) scoring.

### Diagnostic image scoring

One of four radiologists will score each MRI and X-ray using the modified RAMRIS and vdHSS methods, respectively. Radiologists will be blinded to intervention allocation. The images sets will be anonymized and therefore scored independently from other acquisitions for the same patient. The modified RAMRIS or vdHSS adjusted for inter-rater reliability will be compared between the biannual diagnostic imaging time point and baseline, or to the time point when disease progression was last detected. For week 0 MRI, the modified RAMRIS of the worst-affected hand will be used as the reference score to determine changes. Total baseline tender and swollen joint count will determine the worst-affected hand. If joint counts are equal bilaterally, the participants’ self-reported dominant hand will be used to determine the reference score. For X-ray, the vdHSS for both hands and wrists will be compared biannually to monitor disease progression.

The inter-rater reliability across the four participating radiologists for scoring the RAMRIS and vdHSS, respectively, will be determined using baseline imaging data for the first nine study participants. A similar sample of images sets acquired from patients who first complete the 52-week study imaging requirements will be used to determine changes in SDD over time. The inter-rater SDD determined from the baseline sample will be used to determine adjusted modified RAMRIS and vdHSS scores at baseline and 26-week time points. The SDD determined at the 52-week time point will be used to adjust 52-, 78- and 104-week scores.

Changes in modified RAMRIS and vdHSS scores in magnitudes of SDD will be sent to the treating rheumatologist in the form of blinded diagnostic imaging reports for participants allocated to the MRI and X-ray treatment groups, respectively. For participants allocated to the sham-intervention group, negative reports will be sent. The SDD is a measure of the reliability specific to the raters and procedures of this study [58,59]:

(1)$$\mathrm{SDD}=1.96\times \sqrt{\frac{2\times \mathrm{SE}M_{\mathrm{STATUS}-\mathrm{SCORE}}}{k}}$$

OR

(2)$$\mathrm{SDD}=1.96*\frac{SD_{\mathrm{\Delta STATUS}-\mathrm{SCORE}}}{\sqrt{k}}$$

where *SEM*_*STATUS* − *SCORE*_ is the standard error of measurement of the status-score; *SD*_*ΔSTATUS* − *SCORE*_ is the standard deviation of the difference in status-score; *k* is the number of readings over which the analysis is averaged.

Upon detection of an increase in RAMRIS or vdHSS of at least the SDD, a standardized blinded report will be sent to the rheumatologist indicating the status of disease progression for the patient, as follows:where < # > is the difference of the SDD-adjusted score between the two time points of interest rounded down to the whole number.

“Disease progression < # > -fold the smallest detectable difference was detected on < date of current MRI/X-ray > relative to < date of previous MRI/X-ray>. This disease progression consists of evolving synovitis, and/or edema, and/or joint space narrowing, and/or erosive damage.”

This calculation represents multifold differences in SDD. Disease progression reports sent to the rheumatologist will eliminate references to imaging modality, including reference to either RAMRIS or vdHSS, or of imaging features specific to either modality. These considerations will help maintain allocation concealment.

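### Progression from week 52 onward can be computed by subtracting scores scaled with two different SDDs, so a shift in the SDD alone can create or hide it

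*Protocol article*

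**What the plan says.** Under Diagnostic image scoring, the protocol article assigns one SDD to the early visits: "The inter-rater SDD determined from the baseline sample will be used to determine adjusted modified RAMRIS and vdHSS scores at baseline and 26-week time points". It assigns another to the later ones: "The SDD determined at the 52-week time point will be used to adjust 52-, 78- and 104-week scores". Each follow-up score "will be compared between the biannual diagnostic imaging time point and baseline, or to the time point when disease progression was last detected", so a visit at week 52, 78 or 104 may be referred back to week 0 or week 26.

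Under Study design, in the text after Figure 1, the decision rule is: "Differences in SDD-adjusted scores will be used to determine disease progression". The standardized report carries a number that "is the difference of the SDD-adjusted score between the two time points of interest rounded down to the whole number", and the article adds: "This calculation represents multifold differences in SDD". The sentence that introduces the report words the trigger differently: "Upon detection of an increase in RAMRIS or vdHSS of at least the SDD". It does not say which of the two SDDs applies.

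**The concern.** The two SDDs are estimated separately, and nothing in the article re-expresses the reference score on the later SDD. If each score is divided by the SDD of its own period before subtraction, a patient whose score has not moved shows a change as soon as the two SDDs differ. The higher the reference score, the larger the spurious change.

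Two things depend on the rule. It decides which positive reports reach the rheumatologist in the MRI and X-ray groups, and those reports are the intervention. It also feeds imaging progression, which the Primary outcome section names as a co-primary endpoint.

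**Working it through.** **Inputs.** From the article: the assignment of SDDs to visits, the choice of reference visit, and nine image sets per modality read by four radiologists at each of two times. Assumed: the SDD values and patient scores used below, because the article gives none. Inferred: adjusted score = score ÷ SDD, because the difference of adjusted scores is said to be a multiple of the SDD.

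**Algebra.** For a visit t at week 52 or later, with a reference at week 0 or 26:

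adjusted change = S_t/SDD_52 − S_ref/SDD_0.

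If S_t = S_ref = S, this is S(1/SDD_52 − 1/SDD_0). It is zero only if S = 0 or the SDDs are equal. The raw rise needed to reach an adjusted change of 1 is SDD_52(1 + S_ref/SDD_0) − S_ref.

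**Worked cases (assumed SDDs).**
- SDD falls from 8 to 6.4, score 40 at both visits: 40/6.4 − 40/8 = 6.25 − 5.00 = 1.25. The report reads 1-fold progression with no change.
- SDD rises from 8 to 9.6, reference score 40: rise needed = 9.6 × (1 + 5) − 40 = 17.6 points, although the current SDD is 9.6.
- Same SDDs, raw rise of exactly 9.6: the raw-increase trigger fires, but 49.6/9.6 − 40/8 = 0.17, which rounds down to a 0-fold progression report.

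**How far apart the SDDs may be by chance.** Nine sets and four readers give (9 − 1)(4 − 1) = 24 degrees of freedom per estimate in a two-way layout. With constant true reliability, the SDD ratio follows the square root of an F(24, 24) variable, with a 95% range of 0.66 to 1.51. Equation (1) as printed takes the root of the SEM itself. Used that way, the range narrows to about 0.82 to 1.23.

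**Simulation.** 400,000 draws per row; normal reading error; SDD = 1.96 × √2 × SEM; true SDD constant; 24 degrees of freedom per estimate; progression if the adjusted change is at least 1.

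| Reference score (in SDDs) | False progression, two SDDs | False progression, one SDD |
|---|---|---|
| 0 | about 3% | about 3% |
| 1 | 4.2% | 3.1% |
| 2 | 7.2% | 3.1% |
| 4 | 15.7% | 3.1% |
| 8 | about 28% | about 3% |
| 16 | about 38% | about 3% |

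Detection of a true rise of 1.5 SDD is about 83% with one SDD at every level. With two SDDs it is 79% at a reference score of 1 SDD, 75% at 2 and 68% at 4.

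**Scope.** Week 26 against week 0 uses one SDD. So does week 78 or 104 against a reference at week 52 or later. Only comparisons that cross from week 0 or 26 to week 52 or later are affected, which includes those of every patient not yet flagged by week 52.

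**The case against.** The strongest reply is that division by the SDD is inferred. The sentence that says when a positive report is issued speaks of an increase in the score itself of at least the SDD. Read as a raw-score trigger with the later SDD, it never flags an unchanged recorded score, and mainly the fold number is distorted. This stands as a limit on certainty, but it does not remove the problem. The Study design text rests progression on adjusted differences, the report number is defined the same way, and the two wordings can produce a 0-fold report. They need reconciling on either reading.

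It can also be said that the larger rates belong to high scores. That is right: eligibility requires only six weeks of symptoms, some patients may score low, and the effect there is slight. The mix of scores is unknown.

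A reader might infer that 16% to 38% of unchanged patients in this trial will be falsely flagged. The documents do not support that. The rates average over hypothetical SDD pairs, whereas each modality has one realised pair, and if the two are close little happens.

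A reader might also infer that the scaling favours one arm on the co-primary endpoint. Within a modality, all arms are imaged and scored by the same rule, so this misclassification is common to them and mainly dilutes the contrast. DMARD escalation is not calculated from the SDD and is affected only through the reports.

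Finally, the Discussion says the SDD is re-estimated to allow for changing reliability. That is a fair aim, but it is met by choosing the SDD for the threshold, not by scaling the two visits differently.

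**Conclusion.** The rule as written needs correction. On the natural reading of an adjusted score, comparisons from week 0 or 26 to week 52 or later mix two scales. The error is negligible at low scores and grows with the reference score: at 4 SDDs, average false progression is about 16% instead of 3%, and detection of a true 1.5-SDD rise is 68% instead of 83%. In the trial itself the error goes one way within each modality: spurious progression if the SDD falls, missed progression if it rises.

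The figures rest on assumed scores and SDDs, 24 degrees of freedom per estimate, normal error and constant true reliability. They would be smaller with equation (1) as printed. That the adjusted-score and raw-increase wordings conflict, and that no formula is given for the adjusted score, does not depend on these assumptions.

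**What to change.** In Study design and Diagnostic image scoring, define both progression and the reported fold number as

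(raw score at the visit − raw reference score) ÷ SDD in force at the later visit, rounded down,

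with progression when the result is at least 1. Word the report trigger the same way and use the same definition for the co-primary endpoint, so that reports and endpoint agree. An unchanged score then always gives 0, and the re-estimated SDD still serves its purpose as the current threshold. A single SDD pooled over both reliability samples can be a sensitivity analysis.

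The cost is small: a few sentences and a minor programming change, with no new readings. The trial status is ongoing. If reports for week 52 or later have already gone out, record the date on which the rule changed and apply the corrected rule to all visits in the co-primary analysis.

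### Equation (1) for the smallest detectable difference leaves the SEM unsquared under the root, so it disagrees with equation (2), which is offered as its equivalent, unless the SEM equals 1 point

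*Protocol article*

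**What the plan says.** In the protocol article, Diagnostic image scoring, the SDD is defined in two ways, with the word OR between them:

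- Equation (1): SDD = 1.96 × √(2 × SEM / k)
- Equation (2): SDD = 1.96 × SD_diff / √k

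The symbols are explained directly below. The SEM "is the standard error of measurement of the status-score", SD_diff "is the standard deviation of the difference in status-score", and k "is the number of readings over which the analysis is averaged". The same section says how many readings each study image receives: "One of four radiologists will score each MRI and X-ray".

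The SDD is then put to use: "Upon detection of an increase in RAMRIS or vdHSS of at least the SDD, a standardized blinded report will be sent to the rheumatologist". Participants in the sham group get negative reports whatever their images show. Two SDDs are planned per modality. One comes from baseline images of the first nine participants and serves baseline and week 26. The other comes from week-52 images and serves weeks 52, 78 and 104. No value of the SEM or the SDD is given.

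**The concern.** Two formulas presented as alternatives for the same quantity should give the same number, and these do not. The SEM as defined is a standard error, in score points. Under a square root it must appear squared for the result to be in score points. In equation (1) it appears to the first power, so the result is in the square root of score points and cannot properly be compared with a change in score.

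The SDD does three jobs:

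- It decides whether a participant in an active arm is reported as progressing.
- It is the unit of the fold-change figure in that report.
- It defines imaging progression, which feeds the co-primary endpoint.

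Because sham reports are always negative, a wrong SDD would change reports only in the MRI and X-ray arms, and those reports are meant to act on the primary outcome, treatment escalation. The size of the error depends on the SEM. If MRI and X-ray scores have different SEMs, the two active arms would be affected unequally.

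**Working it through.** **Inputs.** Equations (1) and (2), the definitions of SEM, SD_diff and k, and the single reading per image come from Diagnostic image scoring. The four follow-up scans (weeks 26, 52, 78, 104) come from the schedule under Interventions. The SEM is not given, so the values below are assumptions on both sides of 1 point. The article states no SDD, so there is no figure to reproduce. The check is whether the two equations agree.

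**Step 1: relate the two equations.** The difference between two independent readings with the same error has variance SEM² + SEM² = 2 × SEM², so SD_diff = √2 × SEM. Put into equation (2):

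SDD = 1.96 × √2 × SEM / √k = 1.96 × √(2 × SEM² / k)

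Equation (1) as printed, divided by this, is √SEM / SEM = 1/√SEM. The k cancels. The two agree only at SEM = 1.

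**Step 2: value of k.** Each image is read once, so k = 1 for the scores being judged.

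**Step 3: cut-offs and false positives.** For a participant with no true change and normal reading error, the chance that one follow-up scan exceeds the cut-off is 1 − Φ(SDD / (√2 × SEM)). With equation (2) this is 1 − Φ(1.96) = 2.5% for any SEM. With equation (1) as printed it is 1 − Φ(1.96/√SEM). Example for SEM = 4: the cut-off is 1.96 × √8 = 5.54 against 1.96 × √2 × 4 = 11.09, and the false-positive chance is 1 − Φ(0.98) = 16.4%.

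The last two columns give the chance of at least one false positive over the four follow-up scans. They come from a simulation of 400,000 stable participants with one shared baseline reading and independent normal errors.

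| Assumed SEM (points) | Cut-off, eq. (1) | Cut-off, eq. (2) | Per scan, eq. (1) | Per scan, eq. (2) | Any of 4, eq. (1) | Any of 4, eq. (2) |
|---|---|---|---|---|---|---|
| 0.5 | 1.96 | 1.39 | 0.3% | 2.5% | 1% | 8% |
| 1 | 2.77 | 2.77 | 2.5% | 2.5% | 8% | 8% |
| 2 | 3.92 | 5.54 | 8.3% | 2.5% | 22% | 8% |
| 4 | 5.54 | 11.09 | 16.4% | 2.5% | 38% | 8% |

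**Step 4: the fold figure.** At an assumed SEM of 4, a change of 11.1 points is 11.1 / 5.54 = 2.0 SDDs by equation (1) and 11.1 / 11.09 = 1.0 by equation (2). After rounding down, the report would state 2-fold instead of 1-fold.

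**Step 5: after correction.** With SEM² under the root, equation (1) is identical to equation (2), and the per-scan rate is 2.5% whatever the SEM.

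**The case against.** The strongest reply is that this is a misprint with no consequence. Equation (2) is correct, nothing says that equation (1) is the one used for calculation, and no wrong SDD appears anywhere. A superscript could also have been lost in typesetting or in conversion to text. In the Sample size section an expression has dropped out of the sentence on what the standard deviation is inversely related to. This reply stands as far as consequences go: a planned wrong cut-off is not shown. It does not remove the contradiction. The root, fraction, subscripts and k in equation (1) are all intact, and the verbal definition describes a standard error, not a variance, so the formula and its legend cannot be followed together.

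A reader might infer that the cut-off will be far too low and that the active arms will be flooded with false-positive reports. The documents do not support that. It needs both literal use of equation (1) and an SEM well above 1 point, and neither is stated. Below 1 point the error runs the other way and suppresses positive reports.

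A reader might also infer that k could be set to 4, because four radiologists read the reliability sample. The article never says so. Its definition of k, together with one reading per image, already implies k = 1. Confirming k is worthwhile, but k is not an error in the text.

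Two limits on reach also stand. Sham reports do not depend on the SDD. The co-primary endpoint also counts clinical radiology reports from discretionary imaging, so the SDD is not its only determinant. Finally, the rates assume normal errors and one constant SEM, whereas the X-ray score is described as ordinal and the SDD is re-estimated at week 52.

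**Conclusion.** Equation (1) is wrong as written. With the SEM defined as a standard error, it is dimensionally inconsistent and differs from equation (2) by a factor of 1/√SEM for any k. That conclusion rests only on the printed formulas, their definitions, and independent readings with equal error.

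The consequence is conditional. If equation (1) were applied literally with k = 1, the cut-off for positive reports in the two active arms, and for SDD-based progression, would be too low when the SEM exceeds 1 point and too high when it is below 1. Over the assumed SEMs of 0.5 to 4, the per-scan false-positive chance would run from about 0.3% to about 16%, against the 2.5% that equation (2) gives. The documents fix neither the SEM nor the equation used, so neither the direction nor the size can be settled from them. The point still deserves correction because the SDD governs what the active arms receive.

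**What to change.** Correct equation (1) to SDD = 1.96 × √(2 × SEM² / k), which equals 1.96 × √2 × SEM / √k and is identical to equation (2).

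Confirm which form was used for the baseline and week-52 SDDs in each modality, and that k was 1, as the single-reader design implies. If any SDD was derived from the printed equation (1), recompute it before further reports are issued and before the co-primary endpoint is analysed, and record which reports had already gone out under the old value. If equation (2) was used throughout with k = 1, only the printed formula changes.

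The cost is one exponent, a check of at most four numbers (two time points for each of two modalities), and recalculation only where the check fails.
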